**Self-management outcome measures**	
Health Education Impact Questionnaire (heiQ) [71]	
Constructive attitude and approaches	α = 0.81 [71]
Skill and technique acquisition	α = 0.81 [71]
Health Service navigation	α = 0.82 [71]
Positive and active engagement in life	α = 0.86 [71]
Health-directed activities	α = 0.80 [71]
Self-monitoring and insight	α = 0.70 [71]
Health-directed behaviors (caregivers only)	α = 0.80 [71]
Emotional well-being (caregivers only)	α = 0.89 [71]
Health Literacy Questionnaire (HLQ)	
Having sufficient information to manage my health	α = 0.89–0.94
Actively managing my health	α = 0.76–0.88
**PA & exercise outcome measures**	
International Physical Activity Questionnaire [76]	ρ =0.80 [76]
Physical Activity Plan and Intention	---
Multidimensional Self-Efficacy for Exercise Scale (MSES) [78]	
Across dimensions of task, coping, and scheduling	α = 0.83–0.91 [78]
Across time (baseline, 6-weeks, and 12-weeks)	α = > 0.78 [78]
**Dyadic coping outcome measures**	
Dyadic Coping Inventory (DCI) [79]	
Across both patients and partners	α = 0.63–0.84 [80]
°Revised Dyadic Adjustment Scale (RDAS) [82]	α = 0.89–0.95 [83]

^a^ Cronbach’s alpha is interpreted as follows: Excellent (α ≥0.90), Good (α = ≥0.80-0.89), Acceptable (α = ≥0.70-0.79), and Poor (α = <0.70).

° Optional scale for both patients and caregivers to complete

#### Medical Outcomes Study (MOS) 12-item Short Form Health Survey (SF-12) [57]

The SF-12 yields a Physical Component Summary (PCS) and a Mental Component Summary (MCS) score [57]. This scale has been used in other caregiver studies [5, 58, 59]. The scores are calculated using weighted scoring and standardized from 0–100 (US norm mean = 50, SD = 10). Internal consistency of the SF-12 PCS (α = 0.82) and MCS (α = 0.75) have been assessed to be adequate [60] across nine European countries including France [61].

#### Hospital Anxiety and Depression Scale (HADS) [42]

The 14 items on the HADS are equally divided between the HADS-Anxiety and HADS-Depression subscales (α = 0.68–0.93) [62]. Subscale scores of 8 to 10 are categorized as borderline and scores of 11 to 21 as clinical [42]. A recent review identified the HADS as one of the questionnaires of choice to assess anxiety and depression among patients with cancer [63]. A criticism of the HADS, mainly based on classical test theory analyses, is that it is not a dependable means of differentiating anxiety and depression [64]. However, studies by our team using item response theory [65, 66] have supported the ability of the HADS to discriminate between anxiety and depression among patients with cancer and their caregivers. Furthermore, the reliability and discriminant validity of the French Canadian version of the HADS remains high (α = 0.79–0.89) [67].

#### Perceived Stress Scale (PSS) [68]

The PSS consists of 10 items that measure the degree to which participants appraise situations in their life as stressful. Participants are asked about the frequency of their feelings and thoughts during the last month. Each question is rated on a 5-point Likert scale (0 = never, 1 = almost never, 2 = sometimes, 3 = fairly often, 4 = very often). Scores are calculated by reversing the scores (e.g., 0 = 4, 1 = 3, 2 = 2) on the four positive items. A summary score is then calculated by summing all 10 items. The PSS-10 has adequate reliability and validity across numerous studies (α = 0.74–0.91) [69] and in the French language (α = 0.73–0.81) [70].

#### Health Education Impact Questionnaire (heiQ) [71]

The heiQ (Version 3.0) is a 40-item measurement system examining the effects of health education programs on individuals’ self-management skills for coping with a chronic condition [71]. It consists of eight different subscales: (a) positive and active engagement in life, (b) skill and technique acquisition, (c) constructive attitude and approaches, (d) self-monitoring and insight, (e) health services navigation, (f) social integration and support, (g) health-directed activity, and (h) emotional distress [71]. Given the aim of *TEMPO*, patients are given six subscales (subscales: a, b, c, d, e, f), whereas caregivers complete the entire scale. Studies have confirmed its reliability and validity across subscales (α = ≥ 0.70), in the French language (α = 0.69–0.89) [71, 72] and in the cancer setting [73] (α = 0.75–0.90).

#### Health Literacy Questionnaire (HLQ )[74]

The 44-item HLQ assesses health literacy across nine conceptually distinct domains. Patients and caregivers both complete the domains most relevant to *TEMPO*: having sufficient information to manage my health (4 items), and actively managing my health (5 items). The HLQ has been found to possess adequate validity and reliability across these subscales (α = 0.76–0.94) [74] and in the French language (α = 0.77–0.91) [75].

#### International Physical Activity Questionnaire-Short Form (IPAQ-SF) [76]

The IPAQ-SF is a 7-item self-reported measure to assess the frequency and duration of vigorous-/moderate-intensity PA, walking, and sitting respectively. Activities must be performed for at least a duration of 10 min per session, and within the past 7 days to be reported. It has been found to be valid and reliable across 12 countries, with an overall Spearman’s ρ of 0.80 [76].

#### Physical Activity Plan and Intention [77]

The PA plan and intention questionnaire consists of 8 items developed by our team based on recommendations from Ajzen [77]. It aims to capture indicators of (a) participants’ planned PA behaviors (e.g., where, when, what, and how) and (b) participants’ intentions towards increasing their PA and meeting the recommended physical activity guidelines. Participants rate their level of agreement with 4 statements pertaining to planning their PA (e.g., “I have made a detailed plan about where I will engage in physical activity over the next week.”) and 4 statements pertaining to their intentions to carry out their planned behaviors (e.g., “I intend to work towards the physical activity guidelines to meet them in the next four weeks.”). Rating is done on a 7-point Likert Scale (1 = strongly disagree to 7 = strongly agree).

#### Multidimensional Self-Efficacy for Exercise Scale (MSES) [78]

The 9-item MSES measures participants’ self-efficacy for exercise participation. Three questions (all of which begin with the root phrase “How confident are you that you can…”) assess particular aspects of exercise behavior across three dimensions respectively: (a) task (e.g., follow directions to complete exercise), (b) coping (e.g., exercise when you lack energy), and (c) scheduling (e.g., include exercise in your daily routine). Participants rate their level of confidence to complete each item on a 100% confidence scale, ranging from 0 = not confident at all to 100 = completely confident. Studies [78] evaluating the MSES have assessed its reliability and validity to be good across each respective dimension (α = 0.83–0.91) and across time (α = > 0.78 at baseline, 6 weeks and 12 weeks).

#### Dyadic Coping Inventory (DCI) [79]

The 37-item DCI (patients and partners; α = 0.63–0.84) [80] is a self-reported measure that captures how partners support one another in response to individual and collective stressors [81]. Items are rated on a 5-point Likert scale (1 = very rarely, 2 = rarely, 3 = sometimes, 4 = often, and 5 = very often). The eight negative items are reverse coded, and subscale and summary scores are calculated. The DCI has been found to be reliable and valid for use across 25 different languages [81].

#### Revised Dyadic Adjustment Scale (RDAS) [82]

This is a 14-item questionnaire capturing dyadic consensus, satisfaction, cohesion, and affective expression. Cronbach’s alpha across the subscales range from 0.89 to 0.95 [83]. The DAS-revised is a widely used measure of satisfaction with intimate relationships. Completion is optional for both patients and caregivers.

#### Use of Healthcare services and change in employment

This 9-item questionnaire previously developed by the team [84] captures use of (a) consultation with health care professionals, (b) hospital admissions, (c) medications purchased, (d) use of community services, (e) costs related to medical care, (f) change in employment, (g) change in number of hours worked, and (h) performance at work.

#### Follow-up (T2) questionnaire

All patients and their caregivers complete the follow-up questionnaire separately. Along with the same measures included in T1, the T2 questionnaire includes (a) a health services and community-based resources survey to monitor usual care and co-interventions, (b) a *TEMPO* use and acceptability questionnaire based on previous acceptability measures [27, 40, 85], and (c) The System Usability Scale (SUS) [86]. The answers to each item of the *TEMPO* use and acceptability questionnaire will be examined individually and mostly used to guide the exit interviews. The SUS consists of 10 items assessing the usability of a website. Participants rate aspects of the website design on a 5-point Likert scale (1 = strongly disagree to 5 = strongly agree).

#### Dyadic exit interviews

Dyads where at minimum one member returned their T2 questionnaire are invited to participate in a semi-structured, telephone or online (using Microsoft Teams) exit interview. Interview questions focus on overall experience and usefulness, goals set, progress towards achieving goals, time spent on *TEMPO*, and self-management skills learned through *TEMPO*. An RA with training and experience in qualitative methodology as well as familiarity with *TEMPO* conducts the interviews. The interviews are anticipated to last 40–60 min and are audio-recorded and transcribed verbatim.

#### Study log

The following information is collected by the local RAs: (a) number of individuals approached, (b) number of individuals self-referred to the study, (c) number of individuals eligible and ineligible, (d) number of individuals who declined participation (with reason). The overall study log managed by the study coordinator includes (e) number of participants consented and randomized, (f) number of participants who withdrew (with reason), and (g) number of participants who dropped out (with reason).

#### User tracker information

User tracking monitors adherence to *TEMPO*. These data include: number of logins, time spent on each module, number of times logged in each module, modules completed (clicked through the module), and worksheets completed.

### Data analysis

SAS University Edition, STATA 15 and R version 3.1.2 software will be used for data analysis.

#### Feasibility data

Recruitment and refusal rates along with their respective 95% confidence interval will be calculated. The proportion of missing data will also be similarly calculated.

#### Acceptability data

Average score on the SUS will be calculated, where a score of 68 will be considered high [86]. The proportion of patients who withdrew and the 95% confidence interval will be calculated. Adherence will be calculated based on the number of modules patients and caregivers completed. A module will be considered complete if the user clicked through the entire module and spent at least 15 min on it. Adherence will be categorized as non-adherent (1–2 modules completed), moderate adherence (3–4 modules completed), or high adherence (5 modules completed).

#### Clinical significance

An intention-to-treat analysis will be conducted and missing data will be accounted for via multiple imputation. Baseline imbalances across intervention and control groups will be examined for each outcome score. As this is a pilot trial, effect sizes to estimate the clinical significance of the interventions will be calculated by computing differences between two estimated means divided by the pooled standard deviation [32]. In addition, the proportion of participants that improved on the primary outcome measures by at least the minimal clinically important difference (MCID) will be calculated. The MCID for patients with cancer and their caregivers for the HADS and SF-12 are not available; however, validated MCIDs in other populations will be used. For the HADS, the MCID that will be used is 1.5 [87] and for the SF-12 MCS 3.8 [88] and PCS 3.3 [88]. Subsequent inferential statistics will be carried out for exploratory purposes only to inform the planning of the larger trial. In the event that groups are imbalanced at baseline, they will be compared using regression analysis where the baseline scores will be included in the model as a covariate. No corrections will be undertaken for multiple testing due to the exploratory nature of this pilot.

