### Pilot outcomes justifying a larger trial

As a pilot is not suitable for hypothesis testing [28], the focus is on pilot outcomes justifying a larger trial. Given the lack of published benchmarks for feasibility and acceptability, we aim to introduce rigor by nominating the following values:
The pilot procedures will be feasible if (a) eight dyads/month are recruited across sites, (b) refusal rate does not exceed 45%, (c) missing data are less than 10% [29], and (d) protocol infringements are amenable to change.*TEMPO* will be acceptable if (a) attrition in the intervention group does not exceed 25% [30, 31], (b) 75% of dyads adhere to the *TEMPO* modules, and (c) high system usability is reported.An appropriate measure of clinical significance for a pilot is the effect size (ES) [CONSORT for pilots [28]]. A clinically (not statistically) meaningful finding is defined as an ES > 0.2 [32] for the primary outcomes (QOL and anxiety) of interest at 3 months post-baseline compared with those in the control group. As a secondary assessment of clinical significance is that 25% of participants improve on the primary outcomes by at the least the Minimal Clinically Important Difference (MCID).

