### Adverse event and protocol deviation reporting

Any serious adverse event occurring to a research participant will be reported to the lead research ethics committee without delay. Any protocol deviations will be recorded and depending on the nature, will be submitted to the ethics committee as an amendment.

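### The secondary MCID criterion counts only participants who improve, so taken alone it can be met when more participants deteriorate than improve

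*Protocol article*

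**What the plan says.** The section *Pilot outcomes justifying a larger trial* of the protocol article gives two tests of clinical significance. The main one is a between-group effect size: "A clinically (not statistically) meaningful finding is defined as an ES > 0.2 [32] for the primary outcomes (QOL and anxiety) of interest", assessed "at 3 months post-baseline compared with those in the control group". The other is introduced with "As a secondary assessment of clinical significance" and requires that "25% of participants improve on the primary outcomes by at the least the Minimal Clinically Important Difference (MCID"). No arm or comparator is named for this second test.

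Under *Data analysis*, the subsection *Clinical significance* obtains the effect size by "computing differences between two estimated means divided by the pooled standard deviation". For the second test it says only that "the proportion of participants that improved on the primary outcome measures by at least the minimal clinically important difference (MCID) will be calculated". The thresholds are fixed: "For the HADS, the MCID that will be used is 1.5 [87] and for the SF-12 MCS 3.8 [88] and PCS 3.3 [88"]. Neither section mentions participants who worsen by these amounts, and neither sets separate criteria for patients and caregivers. On safety, *Adverse event and protocol deviation reporting* states: "Any serious adverse event occurring to a research participant will be reported to the lead research ethics committee without delay".

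**The concern.** A share of improvers describes one tail of the distribution of change. When individual scores vary widely relative to the MCID, a sizeable upper tail can sit beside an equal or larger lower tail. The 25% target is listed among the results that would justify a larger trial, so what it can and cannot show matters.

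The design makes the other tail relevant. The programme is self-directed and is used by two people whose scores may move differently, and the Discussion describes caregivers as vulnerable. A pilot that reports only improvers leaves unanswered whether one member of the dyad tends to worsen while the other gains, although the T1 and T2 scores needed to answer this are collected from both members in both arms.

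**Working it through.** **The plan's own figure.** The 25% is a nominated threshold without a derivation, so there is nothing to reproduce.

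**Counting bound.** The section *Sample size* targets 20 dyads per group at 3 months, that is 40 individuals per arm. If the rule is applied to one arm, 10 improvers meet it, and nothing in the rule restricts what happens to the other 30.

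**Model.** Let c be the MCID, s the SD of change, and m the mean worsening, with normally distributed change.

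- P(improve by at least c) = 1 − Φ((c + m)/s)
- P(deteriorate by at least c) = 1 − Φ((c − m)/s)
- Setting P(improve) = 0.25 gives m = 0.674s − c

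**Inputs.** The MCIDs are those in *Clinical significance*. The SF-12 SD of 10 is the US norm quoted in the SF-12 section. The alphas of 0.75 (MCS) and 0.82 (PCS) are in Table 3. The SD of change is not given and is assumed:

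- SF-12: s = 10·√(1 − alpha)·√2, that is 10·√0.25·√2 = 7.07 for MCS and 10·√0.18·√2 = 6.0 for PCS. This puts internal consistency in the place of 3-month stability.
- HADS-Anxiety: s = 3.0, range 2.5 to 3.5, with no figure in the document behind it.

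**Results with exactly 25% improved.**

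| Scale | c | s | Mean worsening m | Deteriorated | Deteriorated if mean change is zero |
|---|---|---|---|---|---|
| HADS-Anxiety | 1.5 | 2.5 | 0.19 | 30% | 27% |
| HADS-Anxiety | 1.5 | 3.0 | 0.52 | 37% | 31% |
| HADS-Anxiety | 1.5 | 3.5 | 0.86 | 43% | 33% |
| MCS | 3.8 | 7.07 | 0.97 | 34% | 30% |
| PCS | 3.3 | 6.0 | 0.75 | 33.5% | 29% |

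**Sensitivity.** Take instead s = SD·√(2(1 − r)), with an assumed T1–T2 correlation r of 0.5 to 0.8 and an assumed HADS-Anxiety SD of 3 to 4.5. The deteriorated share at 25% improved is then 30% to 47% for MCS, 36% to 51% for PCS and 18% to 50% for HADS-Anxiety. The 18% arises at SD 3 and r = 0.8, where fewer deteriorate than improve; at SD 3.5 and r = 0.8 the two shares are about equal.

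**Does the effect-size criterion catch this?** For average worsening, yes. Against a stable control, the MCS case gives −0.97/10, about −0.10, and the PCS case −0.75/10, about −0.07. Both fail the requirement of more than 0.2.

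For opposite movement within dyads, not necessarily. Suppose patients and caregivers are pooled, the control arm is stable, and on MCS (SD 10, s = 7.07) patients gain 6.5 on average while caregivers lose 2:

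- Pooled mean gain: (6.5 − 2)/2 = 2.25. The spread between roles adds 4.25² = 18.1 to the TEMPO variance, so the pooled SD is √((118.1 + 100)/2) = 10.4 and the effect size is 2.25/10.4 = 0.22.
- Improved: patients 1 − Φ((3.8 − 6.5)/7.07) = 65%, caregivers 1 − Φ((3.8 + 2)/7.07) = 21%, together 43%.
- Deteriorated: caregivers 1 − Φ((3.8 − 2)/7.07) = 40%, against 30% expected at zero mean change.

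On this scale both thresholds are passed, yet about twice as many caregivers deteriorate as improve.

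**The case against.** The strongest reply is that the 25% rule is only the secondary assessment. The main test compares group means, so every worsening participant lowers it, and feasibility and acceptability are the trial's primary aim. This stands, and it limits the weight of the point. A reader might infer that the pilot as a whole could be judged clinically promising while the average participant worsens. The document does not support that: against a stable control such an arm fails the effect-size criterion.

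A reader might also infer that TEMPO could harm more people than it helps and still pass. That does not follow either. Change from baseline without a comparator cannot separate the programme from disease course, treatment, measurement noise or the pandemic effects on scores that the Discussion anticipates. Much of the tabulated deterioration is what zero mean change would produce: on the SF-12, 29% to 30%, so the 33.5% and 34% exceed it by only 4 to 5 percentage points.

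Nor is worsening unrecorded. The same scales are collected at T2 in both arms and enter the effect size, SF-12 scores feed the QALY comparison, and exit interviews explore experience. What is absent is a count of those who worsen in any stated analysis; serious adverse event reporting does not supply one.

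Finally, a three-way table could be left to an analysis plan that is not shown. That is true of the table, but the article itself fixes the decision rule, in one direction, and a later table would not alter that rule.

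**Conclusion.** The point holds in a limited form. As written, the secondary criterion is one-directional and, taken alone, can be met when more participants deteriorate than improve: 25% against 33.5% to 37% in the central cases. The size rests on normal change scores and assumed SDs of change, and the ordering reverses for HADS-Anxiety when the SD is small and the correlation high. The between-group effect size covers average worsening but, if the two roles are pooled, not opposite movement of patients and caregivers; the role example uses assumed means and shows only that this is possible. This is an inexpensive improvement to a secondary criterion. It is not a flaw in the main test and not a finding of harm.

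**What to change.** In *Clinical significance*, classify each participant on HADS-Anxiety, MCS and PCS as improved by at least the MCID, unchanged, or deteriorated by at least the MCID. Report all three shares with confidence intervals by arm, separately for patients and caregivers, and give the number of dyads in which one member improves and the other deteriorates.

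In *Pilot outcomes justifying a larger trial*, judge the secondary criterion on the differences, TEMPO minus control, in the improved and deteriorated shares. A rule that improvers must outnumber deteriorators within the TEMPO arm would not serve. It is again uncontrolled: it would pass a little under half the time by chance with no true change, and a general pandemic decline could make an effective programme fail it.

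The cost is one more tabulation of collected data and a criterion that is somewhat harder to meet. Precision is low. With shares near 30% and independence assumed, the 95% half-width of a between-arm difference is 1.96·√(2·0.3·0.7/40), about 20 percentage points, for 40 individuals per arm, and 1.96·√(2·0.3·0.7/20), about 28 points, for one role with 20 per arm. The differences should therefore be read as estimates for planning.

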### Sample size

Based on other studies [30, 40] and our data from the initial acceptability of *TEMPO* [26], it is assumed that 40% of dyads approached will be ineligible, 40% will refuse participation, 15% will not return their baseline survey, and 25% will be lost to follow-up. Accordingly, 260 dyads will need to be approached to reach the target sample size 40 dyads (20 per group) at the 3-month follow-up [41].

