### Allocation and randomization

Once dyads submit their baseline survey, they are randomized by the project coordinator using a computer-generated randomization schedule that uses random block sizes of 2 or 4, with an allocation ratio of 1:1, stratified by severity of HADS Anxiety subscale. SAS University Edition is used. The stratification uses the highest HADS score in the dyad categorized as “none” (HADS score < 8), “mild” (HADS score 8–10) or “moderate/severe” (HADS score ≥ 11) [42]. To ensure allocation concealment and prevent selection bias, only the study coordinator can enter the unique participant identifier [43] into the randomization schedule, along with date of baseline completion and HADS scores of both dyad members. An automated interface, programed by the study statistician, assigns the study group.

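### Baseline adjustment hinges on an undefined imbalance check, so the effect sizes judged against 0.2 are data-dependent and less precise than they need be

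*Protocol article*

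**What the plan says.** All the analysis wording is in the protocol article, Data analysis, under Clinical significance.

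- Baseline check: "Baseline imbalances across intervention and control groups will be examined for each outcome score". No test, cut-off or other criterion is given.
- Effect size: obtained by "computing differences between two estimated means divided by the pooled standard deviation". No covariate is named.
- Inference: "Subsequent inferential statistics will be carried out for exploratory purposes only to inform the planning of the larger trial".
- Adjustment rule, placed after the inference sentence: "In the event that groups are imbalanced at baseline, they will be compared using regression analysis where the baseline scores will be included".

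Under Pilot outcomes justifying a larger trial, the effect size is given a decision role: "A clinically (not statistically) meaningful finding is defined as an ES > 0.2", for quality of life and anxiety at three months against control.

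Under Allocation and randomization, dyads are allocated 1:1 in blocks of 2 or 4, "stratified by severity of HADS Anxiety subscale". The stratum is set by the higher score in the dyad, in three levels. The analysis wording does not mention the stratum.

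Under Sample size, the target is 20 dyads per group at three months.

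**The concern.** Whether an outcome is adjusted depends on what the baseline data show, judged by a criterion that the plan leaves open. Anxiety could be reported unadjusted and a quality-of-life score adjusted, or the reverse, and both would then be held to the same 0.2. The choice could be made, or appear to have been made, with results in view.

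The text also does not settle which estimate is held to 0.2. The regression sentence follows the statement that inference is exploratory, so it may govern only those exploratory comparisons and leave the effect size as a plain difference in means. It may equally be meant to supply the means in the effect size.

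Precision is lost as well. In a small trial, chance differences at baseline carry through to the three-month means in proportion to the correlation between the two time points. Regression on baseline removes that component, whether or not the imbalance is large enough to be noticed.

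**Working it through.** **Inputs.** From the documents: 20 dyads per arm at three months, 1:1 allocation, a threshold of 0.2, and randomisation stratified on the dyad's highest HADS-Anxiety category. Not in the documents: the correlation r between a person's baseline and three-month score. I assume 0.5 to 0.7 and show 0.3 to 0.8.

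**The plan's own figures.** The article gives no standard error or interval width to reproduce. The 20 per group comes from this sentence: "260 dyads will need to be approached to reach the target sample size 40 dyads (20 per group) at the 3-month follow-up". The stated losses are "40% of dyads approached will be ineligible, 40% will refuse participation, 15% will not return their baseline survey, and 25% will be lost to follow-up". Applied in sequence they give 0.6 × 0.6 × 0.85 × 0.75 = 0.2295, so 260 approached would yield about 60 dyads. If both 40% losses are shares of those approached, 0.2 × 0.85 × 0.75 = 0.1275 and the yield is about 33. The 260 therefore does not follow from the rates. That is a separate matter; the check below uses the stated target of 20 per group.

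**Step 1: unadjusted effect size, one member type analysed.** SE = √(1/20 + 1/20) = 0.316. The 95% half-width is 1.96 × 0.316 = 0.62. With no true effect, P(ES > 0.2) = 1 − Φ(0.2/0.316) = 26%.

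**Step 2: always adjusting for baseline.** SE = 0.316 × √(1 − r²). Precision is equivalent to 40/(1 − r²) unadjusted dyads. Falls in SE are from unrounded values.

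| r | SE | Fall in SE | Equivalent dyads | P(ES > 0.2), no effect |
|---|---|---|---|---|
| 0.3 | 0.302 | 0.015 | 44 | 25% |
| 0.5 | 0.274 | 0.042 | 53 | 23% |
| 0.6 | 0.253 | 0.063 | 62.5 | 21.5% |
| 0.7 | 0.226 | 0.090 | 78 | 19% |
| 0.8 | 0.190 | 0.126 | 111 | 15% |

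The adjusted SE drops below 0.2 only if r > √(1 − 0.04/0.1) = 0.77. For the SE to fall by 0.2, r would have to be about 0.93.

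**Step 3: chance imbalance.** For a score that is not stratified, such as the SF-12 components, the standardised baseline difference also has SD 0.316. So P(|difference| > 0.2) = 2 × (1 − Φ(0.632)) = 53%. This figure does not apply to HADS-Anxiety.

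**Step 4: effect of the conditional rule on patient HADS-Anxiety.** A simulation used 40 dyads, no true effect, stratified blocks of 2 or 4, and 6,000 trials per setting. Assumed: mean 6.5, SD 4, within-dyad correlation 0.3. Two possible readings of imbalance were tried. Entries are the SD of the estimated effect size.

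| r | Unadjusted | Adjust if p < 0.05 | Adjust if \|d\| > 0.2 | Always adjust | Always adjust, plus stratum |
|---|---|---|---|---|---|
| 0.5 | 0.309 | 0.307 | 0.290 | 0.287 | 0.288 |
| 0.6 | 0.300 | 0.297 | 0.271 | 0.266 | 0.268 |
| 0.7 | 0.288 | 0.285 | 0.245 | 0.238 | 0.239 |

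At r = 0.6 a significance trigger keeps (0.300 − 0.297)/(0.300 − 0.266) = 9% of the available gain. A 0.2 trigger keeps (0.300 − 0.271)/(0.300 − 0.266) = 85%.

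Stratification cuts the SD of the patient baseline HADS-Anxiety difference from about 0.30 to 0.23. Always adjusting therefore gains 0.02 to 0.05 here, against 0.03 to 0.09 in the same simulation without stratification (0.325 to 0.291, 0.330 to 0.269 and 0.328 to 0.243 for r = 0.5, 0.6 and 0.7).

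**Step 5: if patients and caregivers were pooled.** The article does not say. With 40 persons per arm and within-dyad correlation ρ, the unadjusted SE = √((2/40)(1 + ρ)), which is 0.22 at ρ = 0 and 0.27 at ρ = 0.5.

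**The case against.** Four points can fairly be made for the plan.

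First, the total standard error of 0.316 exceeds 0.2, and a reader might infer that adjustment would remove noise larger than the threshold. The documents do not support that. The total comes mainly from 20 dyads per arm, and adjustment lowers it by only 0.04 to 0.09 for r of 0.5 to 0.7. On another measure, the SD of the removable component (r × 0.316), 0.2 is passed only if r > 0.63, and the article gives no r. This objection stands in full.

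Second, a reader might infer that the randomisation stratum is excluded from every model. The article is silent, and a condensed article may leave this to the analysis plan. It also makes no practical difference: with baseline in the model, adding the stratum moves the SD from 0.266 to 0.268 at r = 0.6. This stands too.

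Third, a reader might infer that conditional adjustment recovers little. That holds for a significance trigger and fails for a 0.2 trigger. The supportable complaint is that the plan does not say which applies.

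Fourth, the wording about estimated means could cover model-based, adjusted means; clinical significance is a secondary aim; and inference is declared exploratory. These points limit the consequence. They do not remove the conditional rule, which is stated outright. An analysis plan that followed it would inherit the problem, and the effect size is still listed among the outcomes that justify a larger trial.

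**Conclusion.** The concern holds as a point about an undefined, data-dependent estimator with a moderate loss of precision. The plan adjusts for baseline only after an imbalance check with no criterion, outcome by outcome, and does not make clear whether the effect size compared with 0.2 is adjusted at all.

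The cost in precision is an SE of about 0.32 where about 0.27 to 0.23 is attainable, given 20 dyads per arm and an assumed r of 0.5 to 0.7. It is smaller for HADS-Anxiety, because stratifying on the dyad's highest score already balances each member's own score in part. Pooling both members would lower the starting SE to about 0.22 to 0.27, which is still above 0.2.

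Adjustment does not rescue the 0.2 rule. With no true effect, the chance of passing it falls from 26% to between 23% and 19%. That remaining weakness comes from the sample size. The change is worth making because it removes a choice made after seeing the data and gains precision at almost no cost.

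**What to change.** Delete the condition on imbalance. For every outcome, take the between-group difference from a pre-specified regression of the three-month score on arm and the participant's own baseline score. Divide it by a pooled SD named in advance, state that this is the effect size held to 0.2, and report it with a 95% confidence interval. Baseline differences can still be described, but they should not decide the model. Including the randomisation stratum is optional.

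The cost is one sentence of analysis wording and one model degree of freedom. No new data are needed, since the Follow-up (T2) questionnaire section repeats the baseline measures.
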